### Objectives

The primary aims of this study are to investigate whether medical hypnosis affects pain intensity and the rate of burn wound healing (i.e., re-epithelialization) in acutely burned children. The secondary aims are to investigate if medical hypnosis affects procedural anxiety, biological stress markers (salivary cortisol and salivary α-amylase), and the rate of PTSD symptom development. We hypothesize that use of medical hypnosis for pediatric patients with acute burns will decrease pain intensity, procedural anxiety, and biological stress markers during wound care procedures; improve wound healing times; and decrease rates of traumatic stress reactions compared to a standard care control group.

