### Interventions

Recruited participants are randomized into either (1) the intervention group: medical hypnosis or (2) the control group: standard care immediately prior to their first wound care procedure (i.e., dressing change or application, which may involve cleaning the wound) at the PLPBC:Intervention groupMedical hypnosisMedical hypnotherapy is used with this group after gathering baseline data. Hypnotic induction (i.e., the method for guiding the participant into a hypnotic trance) starts before nursing staff begin the burn wound care procedure and is maintained throughout the procedure. The hypnotic induction is adjusted for the participant’s age, understanding, and communicative capacity as per the clinician’s judgment. After the first hypnotherapy session (concurrent with the participant’s first wound care procedure), a maximum of four additional hypnotherapy sessions are provided during subsequent visits to the PLPBC for wound care procedures. The clinical judgment of the treating hypnotherapist in consultation with the burns nurses and pediatric surgeons is used to determine the total number of hypnotherapy sessions. Aside from the hypnotherapy, all other treatment is administered according to established standard care. Standard care at PLPBC includes administering oxycodone, with the dosage determined by body weight, 0.1 mg/kg orally (Mundipharma Pty. Ltd., Sydney, NSW 2000, Australia); and paracetamol, 150 mg/kg orally (Sanofi-Aventis AUS Pty. Ltd., Macquarie Park, NSW 2113, Australia).Essential elements of medical hypnosisThe medical hypnosis intervention follows five stages: establishing rapport and creating a setting of positive expectancy; slowing breathing and enhancing relaxation; providing suggestions for deepening relaxation and absorption in the hypnotic state; direct hypnotic suggestions for hypnotically induced analgesia, anesthesia, anxiolysis, and rapid healing; and alerting (i.e., bringing the participant out of the hypnotic trance) [46].MaterialsThe medical hypnosis intervention designed for the treatment purposes of this trial has been documented in a manual and can be obtained from the study’s principal investigator on request.ProceduresThis study uses two hypnotic inductions: the Favorite Stories induction [47] (for children less than 7 years old) and the Favorite Place induction [29] (for children 7 years old and older). Once trance is achieved, suggestions for hypnoanalgesia or hypnoanesthesia are given using the Switches method [29, 48] or the Glove Anesthesia method [29] (sometimes referred to as the Magic Glove in the relevant literature). Suggestions for rapid wound healing are also given, and self-hypnosis is taught to the child [29].ProviderThe medical hypnosis provider in this study is a medical student and Research Higher Degree candidate who received group training by the American Society of Clinical Hypnosis (ASCH) and individual face-to-face training with [name], M.D., FACS, ABMH, Professor of Surgery and Psychiatry at Tulane University, New Orleans, USA and former president of both the ASCH and the American Board of Medical Hypnosis.All medical hypnosis is delivered face to face in a clinical consulting room within the PLPBC, LCCH. A minimum of one session and maximum of five sessions of medical hypnosis are provided for each participant in the intervention group, concurrent with their scheduled wound care procedures. Each session lasts for the duration of the participant’s wound care procedure.Although the medical hypnosis manual is adhered to as closely as possible, the intervention is tailored to the participant based on their developmental and chronological age, capacity to focus, distress related to the total burn area and depth, acuity and nature of the burn event, and location of the burn. This adherence allows replication of hypnotherapy procedures used to the extent permitted given that the children and adolescents who participate have varied developmental and chronological ages, presentations, and levels of capacity for focus, as well as distress related to total burn area and depth, acuity and nature of the burn event, and different specific anatomy involved.Control groupStandard careStandard procedural distraction is available to this group, including music, toys, the Ditto™ (Diversionary Therapy Technologies, QLD, Australia) [6] and other electronic devices (e.g., TV, hand-held games, portable DVD players), books, and parental presence. The consulting hypnotherapist is positioned in the procedure room with the participant but does not provide hypnosis to ensure that the only difference is the use of medical hypnosis. The hypnotherapist does not interact with participants in the control group to avoid potentially using hypnotic techniques and is only present to help record outcome measures associated with wound care procedures.

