#### Primary outcome measures

The two primary outcome measures are pain intensity and wound healing (i.e., re-epithelialization time). Pain measurements are taken several times for each participant. The first time point (baseline) is immediately before premedication prior to removal of the wound dressing in clinic. The second time point is immediately after the new dressing is in place; the worst pain is assessed reflecting the maximal pain intensity experienced by the participant during the procedure (retrospective). For the third time point, a final pain assessment occurs to gauge pain intensity immediately after the new dressings are in place and hypnotherapy has ceased. No pain measurements are taken during hypnosis. Assessing pain intensity in this manner effectively gives three time points relative to the procedure: before, during, and after. These measurements take place at each subsequent dressing change until ≥95 % wound re-epithelialization.

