#### Procedural anxiety

The visual analog scale for anxiety (VAS-A) [55, 56] will be used to measure procedural anxiety in children. Self-reported anxiety measures will only be administered to children 8 years old and above. For participants younger than 8 years, the parent will be asked to assess their child’s anxiety using the same scale. The anxiety measurement is obtained prior to premedication and immediately after new dressing application.

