### Data analysis

Data will be analyzed using SPSS 23 (IBM Corporation, Armonk, NY, USA). Descriptive statistics such as the mean and standard deviation, median and interquartile range, and confidence intervals will be used to report the sample demographics (i.e., age, gender, and mechanism of injury) and to summarize outcome measures, as appropriate. Between-group comparisons will be conducted for potential confounding variables for the primary outcomes. Potential confounding variables affecting wound healing that will be examined include burn depth, days taken to present to the PLPBC, ethnicity, mechanism of injury, percent TBSA, age, and gender [25]. Potential confounding variables affecting pain intensity that will be examined include age, the presence/absence of skin grafting, state anxiety (determined by VAS-A), pharmacologic analgesia given immediately before or during wound care procedures, percent TBSA, and days to re-epithelialization [26, 68]. If significant between-group differences are present for potential confounding variables, those variables will be controlled for in the primary analyses. Between-group differences will be investigated using univariate parametric or non-parametric analyses as applicable (e.g., linear regression, Student’s *t* test, or Mann-Whitney *U* test for continuous data and the chi-squared test or Fisher’s exact test for categorical data). All data will be analyzed on the intention-to-treat (ITT) principle as the primary approach. However, a sensitivity analysis will be conducted for data collected as per protocol. A repeated measures analysis will be undertaken using generalized estimating equations (GEEs) [69] including the main effect of treatment group and time on the primary pain and healing outcomes, as well as on the secondary outcomes of procedural anxiety, PTSD, parent satisfaction, and biochemical stress markers.

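### The significance-triggered adjustment rule can bring days to re-epithelialization, the other primary outcome, and other post-randomization variables into the primary pain analysis

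*Protocol article*

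**What the plan says.** Protocol article, Primary outcome measures: "The two primary outcome measures are pain intensity and wound healing (i.e., re-epithelialization time". The Objectives section hypothesizes that hypnosis "will decrease pain intensity, procedural anxiety, and biological stress markers during wound care procedures; improve wound healing times".

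The Data analysis section gives separate lists of potential confounders for the two outcomes. The pain list has age, "the presence/absence of skin grafting, state anxiety (determined by VAS-A"), and "pharmacologic analgesia given immediately before or during wound care procedures, percent TBSA, and days to re-epithelialization [26, 68"]. The healing list has burn depth, days to presentation, ethnicity, mechanism of injury, percent TBSA, age and gender. One rule then governs both lists: "If significant between-group differences are present for potential confounding variables, those variables will be controlled for in the primary analyses".

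On timing, the Interventions section places randomization "immediately prior to their first wound care procedure". For the VAS-A, the Procedural anxiety section says: "The anxiety measurement is obtained prior to premedication and immediately after new dressing application". The Data analysis section does not say which of these ratings, or from which dressing change, serves as state anxiety.

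**The concern.** In a randomized comparison, a variable measured after allocation cannot confound the treatment effect in the usual sense, but it can be a consequence of treatment. Adjusting for such a variable changes what is estimated. The result is no longer the total effect of hypnosis on pain, and the comparison is no longer protected by randomization.

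Days to re-epithelialization is the clearest case, since it is a primary outcome that the protocol expects hypnosis to improve. For this variable, a significant difference between arms is success on the other primary outcome. A positive healing result would therefore change the primary pain model, and it would do so most often when the treatment works as planned. At stake are the estimate, the power and the type I error of one of the two primary outcomes.

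**Working it through.** **1. Status of each variable on the pain list**

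| Variable | Fixed before the first intervention? |
|---|---|
| Age, percent TBSA | Yes |
| VAS-A, first rating before premedication | Yes; a legitimate baseline value |
| VAS-A, after dressing or at later changes | No; anxiety is also a secondary outcome |
| Analgesia before the first procedure | Possibly |
| Analgesia during procedures or before later changes | No |
| Skin grafting | No |
| Days to re-epithelialization | No; primary outcome, hypothesized to improve |

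**2. Inputs (Sample size section)**

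- Healing: difference 3 days, SD 4, so d = 3/4 = 0.75.
- Pain: difference 2 points, SD 2.5, so d = 2/2.5 = 0.80.
- Alpha 0.05, taken as two-sided; power 80%; at least 33 per arm.
- Assumption: the within-arm correlation r between pain and days to re-epithelialization. The document gives no value; 0 to 0.5 is shown.

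**3. The plan's own figure**

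A two-sided t test with d = 0.75 and 80% power needs 28.9, so 29 per group. Then 29/0.9 = 32.2, so 33 per arm and 66 in total. Both stated figures reproduce.

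**4. How often the rule is triggered**

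The rule adds healing time when its between-arm test is significant. The chance of that is the power of the healing comparison: 0.851 at 33 per arm (0.801 at 29). If hypnosis has no effect on healing, it is 5%.

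**5. What adjustment does to the pain effect**

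The slope of pain on healing time within arms is r × 2.5/4. The adjusted effect is the total effect minus this slope times the 3-day difference: 2 − r × (2.5/4) × 3 = 2 − 1.875r. For r = 0.3 this is 2 − 0.5625 = 1.44 points, a loss of 28%.

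**6. The rule as a whole**

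Simulated trials had 33 per arm, one pain score per child, and healing time in the pain model only when its t test gave p < 0.05. The mean estimate below includes the roughly 15% of trials in which the rule does not trigger.

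| r (assumed) | Effect when adjusted | Mean estimate under the rule | Power under the rule |
|---|---|---|---|
| 0 | 2.00 | 2.0 | 84–85% |
| 0.1 | 1.81 | 1.83 | 78% |
| 0.2 | 1.63 | 1.65 | 70% |
| 0.3 | 1.44 | 1.48 | 63% |
| 0.4 | 1.25 | 1.31 | 55% |
| 0.5 | 1.06 | 1.13 | 48% |

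Without adjustment the estimate is 2.0 points and the power 89% at every r.

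**7. Type I error**

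Suppose hypnosis shortens healing by 3 days and has no effect on pain. The adjusted contrast is then centred on 1.875r points in the direction of harm, not on zero. Under the rule the null hypothesis for pain is rejected in about 8% of trials at r = 0.2 and about 32% at r = 0.5, against a nominal 5%.

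**The case against.** **The adjustment is conditional.** This is true and limits the claim. A reader might infer that the pain analysis always adjusts for healing time. The text adjusts only after a significant difference, and if hypnosis does not affect healing that happens in about 5% of trials. Under the design's own assumptions, however, the condition is met in about 85%.

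**Not every listed variable is a consequence of treatment.** A reader might infer that all the contested variables can be changed by hypnosis. The documents do not support that. The first VAS-A is taken before premedication, and hypnosis begins after baseline data are gathered, so that rating is sound. Analgesia before the first procedure may be sound too. For VAS-A the fault is ambiguity. For grafting and analgesia during procedures, the timing is clear but the protocol states no hypothesis that hypnosis changes them.

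**The two primary outcomes are still assessed separately on the healing side.** This stands. The healing list contains neither pain nor any other outcome, so the dependence runs one way.

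**An unadjusted contrast may also be reported.** The same section mentions univariate comparisons and a GEE model with treatment group and time. That does not cure the rule, which is written for the primary analyses, and no sentence makes an unadjusted pain contrast primary.

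**The magnitude is illustrative.** This stands. The correlation is assumed, and one pain score per child stands in for repeated scores analysed by GEE. At r = 0 there is no bias, and the drop from 89% to about 84–85% power comes from collinearity between healing time and arm, so the other power losses are not bias alone. The direction is attenuation if slower healing goes with more pain; a common cause of both could bias the estimate differently. Still, the protocol lists healing time because it is thought to affect pain, which sits badly with r = 0.

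**A statistical analysis plan may handle this.** The point is a rule that the article states, and a later plan would have to contradict it.

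**Conclusion.** Wrong as written, and to be corrected before analysis. The firm part needs no assumed correlation: the rule allows a primary outcome, known only after randomization and expected to improve under hypnosis, to become a covariate in the primary analysis of the other. With the plan's own effect sizes it does so in about 85% of trials.

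The size of the damage rests on the assumed r. Between r = 0.1 and r = 0.5 the mean pain estimate is about 1.83 to 1.13 points where the total effect is 2, and power is about 78% to 48% where 89% is available. At r = 0 only the small loss of power remains. The inflation of type I error applies where hypnosis affects healing but not pain.

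Grafting and analgesia during procedures share the timing fault, but no size can be put on their effect from the document. The VAS-A item needs its time point stated.

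**What to change.** In the Data analysis section:

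- Remove from the adjustment set of the primary pain analysis: days to re-epithelialization, skin grafting, analgesia given during procedures or before later dressing changes, and every VAS-A rating other than the first pre-procedure one.
- Delete the rule that adjusts when a between-group difference is significant.
- Name in advance the covariates fixed before the first intervention, for example age, percent TBSA and the first pre-procedure VAS-A. Baseline FPS-R is an option, not needed to cure the fault.
- Report healing, grafting and analgesic use by arm. Label any pain model that contains them exploratory.

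The cost is a change of analysis wording. No new data and no further participants are needed.

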### Eligibility criteria for participants

Eligible participants are children aged between 4 and 16 years (inclusive) who meet the inclusion criteria of (1) an acute burn of any depth (excluding erythema only) and (2) presentation to the PLPBC for treatment (inpatient or outpatient). Children are excluded from the study if they are non-English speaking; cognitively impaired; under the care or investigation of the Department of Communities, Child Safety, and Disability Services; on ventilator support; or if they have initial burn wound care procedures carried out in the operating room under general anesthesia.

Patients of the PLPBC are identified by the center’s research manager, and participants’ eligibility is assessed by the nursing staff. All eligible patients presenting to the PLPBC are approached and invited to participate in this RCT by a clinical research team member not involved in their primary care. Parent (the term *parent* includes *legal guardian*) informed consent is obtained and recorded. Child consent is obtained for all children able to read and write. Verbal assent is obtained for all other eligible children.

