### Demographic and clinical information

Participant demographics and medical history are recorded from the caregiver and hospital chart: mechanism and site of injury, estimated percentage total body surface area (TBSA) of burn, burn depth, any first aid treatment applied, and medication given. TBSA is determined by a consultant surgeon using the Lund and Browder method [67].

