### Sample size

A sample size estimate was derived from the primary outcomes: days to re-epithelialization and pain. Based on re-epithelialization within 15 (SD = 4) days and a minimum clinically important difference (MCID) of 3 days [26], the sample size required was estimated as 29 per group, using 80 % power and an α of 0.05. Allowing for 10 % loss to follow-up, a total of 66 participants will be required. Additionally, this sample size is adequate to show an MCID of 2 (SD 2.5) in the pain outcome measures [26]. Recruitment will continue until at least 33 participants in each arm have been obtained with complete data for the primary outcomes.

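### The healing analysis adjusts only for covariates that differ significantly between arms, so strong predictors of healing are usually left out and available precision is lost

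*Protocol article*

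**What the plan says.** The Data analysis section of the protocol article gives a list for healing: "Potential confounding variables affecting wound healing that will be examined include burn depth, days taken to present to the PLPBC", followed by ethnicity, mechanism of injury, percent TBSA, age and gender, seven in all. These are compared between arms, and then: "If significant between-group differences are present for potential confounding variables, those variables will be controlled for in the primary analyses". Otherwise the between-group comparison is univariate, with linear regression, the t test and the Mann-Whitney test given as examples. A GEE analysis of healing is also planned, with treatment group and time as the named effects.

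The last part of the same section adds analyses stratified by burn depth and by age, and regression and GEE models for the influence of clinical factors on the outcomes. It does not say that either is the primary healing test.

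Three other sections bear on the point:
- Randomization describes simple randomisation and no stratification.
- Eligibility admits "an acute burn of any depth (excluding erythema only") and states no limit on days since injury.
- Demographic and clinical information shows that the covariates are already recorded: "estimated percentage total body surface area (TBSA) of burn, burn depth".

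**The concern.** In a randomised trial a baseline difference between arms is due to chance, so its p-value does not show which covariate belongs in the model. What matters is how strongly the covariate predicts the outcome. The protocol names its candidates because it expects them to affect healing, and then leaves each one out unless it happens to cross p < 0.05. Simple randomisation does nothing to balance them by design.

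Two things are at stake. The healing comparison gives up precision that the recorded data could supply. And the analysis model is fixed only after the baseline tests are run. If the unadjusted test were the Mann-Whitney, a triggered adjustment would also force a change of method, because that test takes no covariates.

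**Working it through.** **Inputs from the protocol (Sample size).** "Based on re-epithelialization within 15 (SD = 4) days and a minimum clinically important difference (MCID) of 3 days"; "using 80 % power and an α of 0.05"; "the sample size required was estimated as 29 per group"; 10% loss, 66 in total, and at least 33 per arm with complete primary-outcome data. Sidedness is not stated. Two-sided is assumed, because a one-sided test gives 22 per group and does not reproduce 29.

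**Step 1: the plan's own figure.** The normal approximation gives n = 2(1.96 + 0.84)² × 4²/3² ≈ 27.9, so 28 per group. The exact t-test calculation gives power 0.787 at 28 and 0.801 at 29, so 29 per group is reproduced. Then 29/0.90 = 32.2, so 33 per arm and 66 in total. With 33 complete per arm, unadjusted power is 0.851. No covariate enters any of this.

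**Step 2: how often the rule omits covariates.** Each is omitted with probability 0.95. If they are independent, depth, TBSA and presentation delay are all omitted in 0.95³ = 86% of trials, and all seven in 0.95⁷ = 70%.

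**Step 3: what adjustment would gain.** Fixed adjustment reduces the residual SD from 4 to 4√(1 − R²). R² is not in the protocol, so a range is assumed: the residual SD is 3.79, 3.58, 3.10 and 2.53 days at R² = 0.1, 0.2, 0.4 and 0.6. The simulation assumes a 3-day difference, SD 4, independent normal covariates, seven tested and three prognostic. Approximate power:

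| Assumed R² | 29 per arm, stated rule | 29 per arm, always adjusted | 33 per arm, stated rule | 33 per arm, always adjusted |
|---|---|---|---|---|
| 0.1 | 80% | 83% | 85% | 88% |
| 0.2 | 79% | 86% | 84% | 90% |
| 0.4 | 81% | 94% | 86% | 97% |
| 0.6 | 82% | 99% | 87% | over 99% |

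Repeat runs agree to about one or two points. The gain at R² = 0.1 is therefore about 2 to 3 points and should not be read more finely. The rule itself gains at most about 2 points over never adjusting.

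**Step 4: type I error.** Under the rule it is about 3.4–4.9% and falls as R² rises. Under fixed adjustment it stays at about 5%.

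**Step 5: chance imbalance.** At 33 per arm, an imbalance up to about 2.00 × √(2/33) = 0.49 SD is non-significant and goes unadjusted. The SD of the imbalance is √(2/33) = 0.25, so one of 0.4 SD or more in a given covariate occurs in about 10% of trials. If that covariate correlates 0.5 with healing days (assumed), 0.4 SD shifts the estimate by 0.5 × 4 × 0.4 = 0.8 day, against a 3-day target difference and an unadjusted standard error of 4 × 0.246 = 0.98 day.

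**Step 6: timing of the depth reading.** Interventions places randomisation immediately before the first wound care procedure and starts hypnotic induction before nurses begin. Outcomes places the laser Doppler depth measurement at the first dressing change. That reading is therefore made after randomisation and, in the intervention arm, after hypnosis has started. Blinding states that it is assessed blind, but that does not make it a baseline value.

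**The case against.** The strongest reply is that nothing essential fails. The trial reaches its planned power without covariates, and recruitment to 33 complete per arm gives about 85%. The test does not exceed 5%. Depth and age are covered by planned stratified analyses, and linear regression, which accepts covariates, is among the listed methods. The gain depends on an R² that the protocol does not give. The eligibility criteria also exclude ventilated children and those whose initial wound care is done under general anaesthesia in the operating room, which may narrow the range of severity and make a high R² doubtful.

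Most of this stands, and it limits the point. It rules out four stronger readings that a reader might infer:
- **Inflated false positives.** Choosing the model from the data suggests this, but here the rule is conservative. It is the model that depends on the data; the error rate is a property of the procedure.
- **An underpowered trial.** The sample size reproduces. The loss is of extra power, not a shortfall.
- **A biased estimate.** Under randomisation the unadjusted estimate is unbiased on average. The 0.8-day shift is a tail case, smaller than one standard error, and that variation is already in the standard error. It largely restates the loss of precision.
- **Burn depth ignored.** The stratified analyses do address it.

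The reply does not rescue the rule. The stratified and regression analyses do not make depth a fixed term in the primary healing test. If they were meant to, they conflict with the conditional rule. Percent TBSA and presentation delay have no stratified provision at all. The possible change of method is a minor point, since Mann-Whitney is only one of the examples.

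**Conclusion.** The point holds as a matter of efficiency and pre-specification. The stated rule leaves each listed healing covariate out about 95% of the time, recovers almost none of the power that adjustment offers, and fixes the model only after the data are seen. At 33 per arm, fixed adjustment would add about 3 points of power at R² = 0.1, 6 at 0.2, 11 at 0.4, and 12 or more at 0.6. So the gain is small if the covariates predict weakly and material if they predict moderately or strongly.

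These figures rest on assumed R² values, independent normally distributed covariates and a two-sided test. The conclusion that the trigger is the wrong criterion needs none of those assumptions. The planned 80% power and the 5% error limit are not in question. The change is worth making but is not critical. The pain covariate list raises separate issues and is outside this point.

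**What to change.** In Data analysis:
1. Delete the significance-test trigger for the healing outcome.
2. State that the primary healing comparison uses a model that takes covariates, for example the linear regression already listed, and is always adjusted for percent TBSA, days from injury to presentation and burn depth, whatever their observed balance.
3. Name the depth record to be used. Take it from an assessment made before randomisation, or justify using the blinded laser Doppler reading despite its timing.
4. State how the depth-stratified analyses relate to the primary test, so that depth has one defined role.
5. Report baseline characteristics by arm descriptively, without p-values.

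This is a change of wording, made before any comparison by arm. The variables are already collected. The cost is a few degrees of freedom and a simple rule for a missing depth value.

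### As worded, the pain GEE may average the untreated pre-procedure rating into the treatment effect; that rating should be a prespecified covariate, not an outcome level

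*Protocol article*

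**What the plan says.** All references are to the protocol article.

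- **Primary outcome measures.** Pain is rated before premedication (labelled baseline), then retrospectively as worst pain during the procedure, then after the dressing is on and hypnotherapy has stopped. The section sums this up: "Assessing pain intensity in this manner effectively gives three time points relative to the procedure: before, during, and after". The set is repeated at every dressing change until healing.
- **Pain.** Child-reported FPS-R is the primary pain measure.
- **Interventions.** Hypnosis begins only once baseline data have been gathered. Self-hypnosis is also taught, and up to four further sessions may follow.
- **Data analysis.** The GEE is described as "including the main effect of treatment group and time on the primary pain and healing outcomes", and the same sentence extends it to anxiety, PTSD, parent satisfaction and stress markers. It names no group-by-time term, no contrast at a particular rating and no primary pain time point. Univariate between-group tests are also planned, again without saying which pain rating they use.
- **Data analysis, covariates for pain.** The list is age, skin grafting, state anxiety, analgesia, TBSA and days to re-epithelialization. These enter only if the arms differ significantly. Baseline pain is not listed.
- **Sample size.** For pain, "this sample size is adequate to show an MCID of 2 (SD 2.5) in the pain outcome measures".

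**The concern.** In a model with main effects of group and time only, the group coefficient is one common between-arm difference. With balanced data it equals the average of the differences at the separate time levels. If the pre-procedure rating is one of those levels, then at the first dressing change the average includes a difference whose expected value is zero, because hypnosis has not started.

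The coefficient would then not describe procedural pain, and it could not be set directly against the 2-point MCID. A treatment that truly lowers pain by 2 points during and after the procedure would be reported as lowering it by less than the MCID, usually with less power. The rating that causes the dilution is also one that could sharpen the comparison as a covariate, and the plan does not list it for that use.

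**Working it through.** **The plan's own figures.** Healing: "Based on re-epithelialization within 15 (SD = 4) days", "a minimum clinically important difference (MCID) of 3 days", "using 80 % power and an α of 0.05". The standardized difference is 3/4 = 0.75. The two-sided two-sample t-test solution is 28.9, so 29 per group, which agrees with "the sample size required was estimated as 29 per group". Allowing 10% loss, 29/0.9 = 32.2, so 33 per arm and 66 in total, as stated. For pain, 2/2.5 = 0.80, and a two-sided t-test has power 85% at 29 per arm and 89% at 33. The sizing arithmetic is sound. It describes an undiluted 2-point difference in a single rating.

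**Inputs.** From the Sample size section: 33 per arm, SD 2.5, difference 2. Assumed, because the article does not give them: a two-sided test, equal SD at each rating, and a common correlation ρ between a child's ratings, shown at 0.3, 0.5 and 0.6. The calculation covers one visit with three ratings.

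**Model A: group main effect over before, during and after.** With true differences of 0, 2 and 2, the estimate is (0 + 2 + 2)/3 = 1.33, whatever ρ is. The SD of a child's mean rating is 2.5·√((1 + 2ρ)/3).

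**Model B: worst (during) rating with the pre-procedure rating as covariate.** The estimate is 2.0. The residual SD is 2.5·√(1 − ρ²).

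| ρ | SD, A | 1.33/SD | Power, A | SD, B | 2/SD | Power, B |
|---|---|---|---|---|---|---|
| 0.3 | 1.83 | 0.73 | 83% | 2.38 | 0.84 | 92% |
| 0.5 | 2.04 | 0.65 | 74% | 2.17 | 0.92 | 96% |
| 0.6 | 2.14 | 0.62 | 70% | 2.00 | 1.00 | 98% |

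**Where A falls below a single unadjusted rating.** A has less power than the 89% benchmark once 1.33/SD drops below 0.80, that is when (1 + 2ρ)/3 exceeds 4/9, so for ρ above 1/6 (about 0.17). Below that, averaging three ratings gains more precision than the dilution costs. The estimate is still 1.33 rather than 2.

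**If the effect fades after the procedure.** Differences of 0, 2 and 1 give an estimate of 1.00 and power of 59%, 50% and 46%. Differences of 0, 2 and 0 give 0.67 and power of 31%, 26% and 24%.

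**Simulation check.** An exchangeable GEE was simulated with 33 per arm and 600 runs per setting, with differences 0, 2 and 2. The main-effects model gave estimates of about 1.32 and power of 85%, 76% and 68% at ρ = 0.3, 0.5 and 0.7. Moving the pre-procedure rating to the covariate side and fitting during and after together gave about 2.01, with power of about 99% or more.

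**Later visits.** If the pre-procedure rating itself carries an effect b, Model A estimates (b + 4)/3. For b = 1 that is 1.67, and for b = 2 there is no dilution. The one-third shrinkage therefore applies to the first dressing change and is an upper limit for later ones if b lies between 0 and 2.

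**The case against.** The strongest counter-argument is that the article does not say the three ratings are levels of time. Time is undefined in the GEE sentence. For healing and parent satisfaction, which the same sentence covers, it can only mean the dressing-change visit. The word introducing the main effects does not exclude an interaction, and the section goes on to allow Šidák-adjusted comparisons, which would suit contrasts at single time points. Univariate two-group tests are also planned, and a two-group comparison is what the pain sizing describes. Finer model terms are often left to a statistical analysis plan, which is not shown.

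Most of this stands and makes the point conditional. A reader might infer that the plan definitely pools all three ratings, or that the primary pain analysis is bound to miss a real 2-point effect. The documents support neither. Even the diluted model has about 83% power at ρ = 0.3 with a sustained effect, and the 24% to 31% figures require no effect at all on the after rating.

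The gap is not removed, however. For pain, the article itself uses time point for before, during and after, so the diluting reading is the natural one. If time means the visit, the plan still does not say which of three ratings is the outcome, and the univariate tests leave this open too. On either reading, baseline pain is missing from a covariate list that the article does give.

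It is also fair to object to making the first dressing change the sole primary time point. That would change the estimand in a trial with repeated sessions and an expected cumulative effect. The correction does not need it.

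**Conclusion.** The point holds in conditional form. If time means before, during and after, and no interaction is fitted, the group coefficient at the first dressing change is shrunk by one third, from 2.0 to about 1.33, when the effect is equal during and after. The shrinkage does not depend on the correlation. The power does: about 70% to 83% for assumed correlations of 0.6 down to 0.3, against 89% for a single unadjusted rating and 92% to 98% for worst pain adjusted for baseline. These figures are for one visit with 33 per arm, SD 2.5 at each rating and a two-sided 5% test. Over the whole course the dilution may be smaller, because later pre-procedure ratings can reflect earlier sessions.

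Whichever meaning of time was intended, the pain effect is not tied to a rating, and an already collected prognostic measurement is not prespecified as a covariate. The sample size calculation itself is not in error.

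**What to change.** Keep the GEE across dressing changes and specify for pain:

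1. The treatment effect is the between-arm difference in worst (during) FPS-R.
2. The after rating is handled as a separate contrast, or through a group-by-time term.
3. Each child's first pre-procedure FPS-R enters as a prespecified covariate, whether or not the arms differ on it, and is removed from the outcome levels.
4. Time is defined explicitly for each outcome: rating within procedure, dressing-change visit, or both.

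The cost is analysis-plan wording, settled before unblinded analysis. All the ratings are already collected, and neither the visits nor the sample size change. Naming the first dressing change as the sole primary time point is optional. It would give an undiluted comparison at a visit every child has, but would make the later visits supportive only, so it should be decided as a question about the estimand.
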